### Provisions for post-trial care {30}

N/a.

#### Outcomes {12}

All outcome measures will be conducted by the researchers, blind to group allocation, after 1 week (baseline), 6 weeks (mid-intervention), and 12 weeks (post-intervention). The demographic information of the participants, including age, sex, and clinical information such as stage of PD and medication reported, will be collected from the participants.

### Primary outcome measures

## Dynamic postural stability

COM-COP separation distance in the anterior–posterior (A-P) and M-L directions. The separation distance of the body’s COM and COP will be determined through motion analysis of walking and obstacle crossing trials to reflect the body’s dynamic postural stability.Clearance distance of the toe and heel. The clearance distance of the toe and heel will be measured from the position of the foot to the height of the obstacle during obstacle crossing. This parameter indicates the dynamic postural stability.

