**Methods/design:**

A single-blind, randomized control trial of 40 individuals with early-stage PD was conducted (Hoehn and Yahr stages 1 to 3). Patients with PD will be randomly assigned to either the TC or control group. The TC group will participate in a biomechanical-based TC training program that is formed based on the movement analysis of TC and will be practiced thrice a week for 12 weeks. The control group will be required to engage in at least 60 min of regular physical activity (PA) on their own for three times per week for 12 weeks. The primary and secondary outcomes will be assessed at baseline and at 6 and 12 weeks after commencing the study protocol. The primary outcome measures will include dynamic postural stability indicated by the center of mass and center of pressure separation distance and clearance distance of the heel and toe measured during fixed-obstacle crossing. The secondary measures are gait speed, cadence, step length during level surface walking (simple task), and fixed-obstacle crossing (challenging task). The Unified Parkinson’s Disease Rating Scale, single leg-stance test with eyes open and closed, and three cognitive scores (Stroop Test, Trail Making Test Part B, and the Wisconsin Card Sorting Test) were also employed.

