### Sample size {14}

The estimated number of participants to achieve the study’s objectives is 40, calculated to attain a 93% statistical power in the difference between two means of the independent variables for testing hypotheses with an alpha level of 5% and a minimal clinical important difference (MCID) of 1.13. This estimation is based on the calculation of the minimal clinical important difference that was determined based on the values obtained in past published studies [13, 26–28]. Considering a 10% of dropout rate of the participants recorded from a previous 24-week TC intervention study for those with PD [13], a 5% dropout rate is expected.

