## Statistical methods

### Statistical methods for primary and secondary outcomes {20a}

Statistical analysis will be performed using SPSS 20.0 and Microsoft Excel 2019 software. Each of the measures will be expressed as mean ± standard deviation. If a measure is not normally distributed, the median and IQR will be calculated to characterize the non-normal distribution. The stratification factors (i.e., age and gender) will be accounted for by an appropriate adjustment technique, such as ANCOVA or multivariable regression analysis. Analysis will be performed to the measures obtained from baseline and at 6 and 12 weeks after TC training. Then, the data between the TC and PA groups will be compared. Two-way analysis of variance (group × time) with repeated measures will be used for examining the effect of TC training on the primary and secondary outcomes. The participants will be analyzed based on their initially allocated groups via randomization, regardless of whether they adhere or if they received the allocated intervention. Statistical significance will be set at *p* less than 0.05.

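### Four to six primary measures share one p < 0.05 threshold with no lead measure, success rule or adjustment, while the 93% power is for a single test at 5%

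*Protocol article*

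**What the plan says.** - **Primary outcome measures, Dynamic postural stability:** the first primary outcome is "COM-COP separation distance in the anterior–posterior (A-P) and M-L directions", and it "will be determined through motion analysis of walking and obstacle crossing trials". The second is toe and heel clearance, measured over the obstacle only.
- **Abstract, Methods/design:** the primary outcomes are COM-COP separation and "clearance distance of the heel and toe measured during fixed-obstacle crossing".
- **Objectives {7}:** the hypothesis names walking speed, mediolateral (M-L) stability, and toe and heel clearance. Walking speed is a secondary outcome. Anterior–posterior (A-P) separation, a primary one, is absent.
- **Statistical methods {20a}:** a two-way repeated-measures ANOVA "will be used for examining the effect of TC training on the primary and secondary outcomes". One threshold follows: "Statistical significance will be set at *p* less than 0.05".
- **Sample size {14}:** 40 participants give 93% power for a difference between two means, "with an alpha level of 5% and a minimal clinical important difference (MCID) of 1.13".

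No section names a leading measure, a testing order, a requirement that all measures succeed, or an adjustment for several tests.

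**The concern.** The main aim is an effect of Tai Chi on dynamic postural stability. The outcome section presents each type of measure as an indicator of that construct. With several such indicators, one threshold and no decision rule, a single nominally significant result could be reported as a positive primary finding. The chance of that happening when there is no effect exceeds the 5% on which the sample size is based.

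The primary set is also described in three different ways. That leaves room to decide, once the data are known, whether level-walking COM-COP or A-P separation belongs to it. In a trial of 20 per arm, where one chance result can carry the conclusion, this matters.

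**Working it through.** **Counting the measures.** COM-COP: 2 directions × 2 tasks = 4. Clearance: toe and heel = 2. Total 6. If only obstacle crossing counts, 2 + 2 = 4.

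**The plan's own power figure.** Inputs are 40 participants, 1:1 allocation (20 per arm), alpha 5% and a difference of 1.13. Two assumptions are needed: the test is two-sided, and 1.13 is a standardised difference, since no unit or SD is given. For a two-sample t-test the noncentrality is d × √(n/2) = 1.13 × √10 = 3.57, with 38 degrees of freedom. Power is 93.6% (94.7% by normal approximation). The stated 93% therefore reproduces, as the power of one test at an unadjusted 5%. With 5% dropout (20 × 0.95 = 19 per arm) it is 92.3%.

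**Familywise error if any one significant measure counts.**

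Under independence it is 1 − 0.95^k:
- k = 4: 1 − 0.8145 = 18.5%
- k = 6: 1 − 0.7351 = 26.5%

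Under a common correlation, from 400,000 simulated sets of two-sided z-tests at 0.05:

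| Correlation | 4 measures | 6 measures |
|---|---|---|
| 0 | 18.5% | 26.5% |
| 0.3 | 17.5% | 24.2% |
| 0.5 | 15.6% | 20.7% |
| 0.8 | 11.4% | 13.9% |
| 0.9 | 9.3% | 10.8% |

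**Power per measure at an adjusted level** (same t-test, d = 1.13):

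| Alpha | 20 per arm | 19 per arm |
|---|---|---|
| 0.05 | 93.6% | 92.3% |
| 0.05/4 = 0.0125 | 82.3% | 79.8% |
| 0.05/6 = 0.0083 | 77.9% | 75.0% |

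**If instead all measures had to succeed.** The false positive rate would not exceed 5%, but 93% would no longer be the trial's power. With d = 1.13 on every measure and independence, power is 0.936^4 = 77% for four measures and 0.936^6 = 67% for six. Positive correlation would raise these figures, to at most 93.6%.

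All power figures use the two-sample comparison on which the sample size is built, not the planned ANOVA.

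**The case against.** **Silence is not a decision.** A 0.05 level is compatible with adjusted p-values, and multiplicity detail is often left to an analysis plan that is not shown here. This stands in part: the article does not say that one positive result is enough. But it does fix several primary measures, a single threshold for all of them, and a power figure for one test at 5%. A later adjustment would leave the quoted 93% without a basis.

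**The written hypothesis is conjunctive.** Objectives {7} joins its components with 'and', and if all were required the error would not be inflated. That passage is not a decision rule, however. It includes a secondary outcome and omits a primary one, so it cannot serve as the success criterion for the listed primary set.

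**The abstract may not conflict with the outcome section.** A reader might infer a flat contradiction, four measures against six. The words about fixed-obstacle crossing can attach to clearance alone, and then the two sections agree. The 3-D motion capture section also treats level walking as a reference task, so six is an upper bound. What remains is ambiguity, not a proven contradiction.

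**Visits.** A reader might infer that measuring at both 6 and 12 weeks inflates the error further. The stated test does not support this: the group by time interaction is one omnibus test per outcome. Visits would add to the error only if tested separately, which the article does not plan.

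**Correlation.** Toe and heel clearance come from the same crossings and may correlate strongly. This stands, and it is why the range must extend to 0.8 to 0.9.

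**Conclusion.** The point holds. The article names four to six primary measures of equal standing, tests each at p < 0.05 without a rule for combining them, and bases its power on one test.

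On an any-one-counts reading the familywise error lies between about 9% and 26.5%, roughly two to five times the nominal 5%. The size depends on two things the article does not give: the success rule and the correlations between measures. A reader might infer that the true error is simply 15% to 27%. That covers only independence to moderate correlation and takes the success rule for granted, so it should not be stated as a property of the plan.

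The need for a correction does not depend on the exact figure. Every correlation examined gives an error well above 5%, and an all-must-succeed rule would instead generally lower the 93% power.

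**What to change.** 1. State one primary set in the same terms in the abstract, Objectives {7} and the outcome section. Two workable forms are:
   - the four obstacle-crossing measures (COM-COP separation A-P and M-L, toe clearance, heel clearance) at week 12, tested with Holm at a familywise two-sided 5%; or
   - a single primary, for example M-L COM-COP separation during obstacle crossing at week 12. The hypothesis already singles out that direction.
2. Make level-walking COM-COP separation and all week-6 results secondary, and say which between-group comparison from the model gives the week-12 result.
3. Say in Statistical methods {20a} that 5% is the familywise level for the primary set.
4. Restate power in Sample size {14}. With Holm on four measures, the strictest step has about 82% power with 20 per arm and about 80% with 19. With a single primary, the 93% stands (about 92% with 19).

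The change is one of wording and needs no extra participants or measurements. The cost of the Holm option is the lower quoted power. The cost of the single primary is that the other measures become supportive only.

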### Secondary outcome measures

## Gait performance

Gait speed. This is a measure of how quickly an individual can walk within a specified distance. Gait speed is a global measure of functional capacity, mobility, and movement performance.Cadence. This measure is defined as the total number of full gait cycles that is completed over a period. In human movement analysis, this gait cycle is defined as the repeated instances of subsequent foot contacts of the same foot. Cadence can reflect the quality of the timing and frequency of the movement. A good stepping or walking cadence can reflect the individual’s movement capacity and their body’s ability to maintain rhythmicity during movement.Step length. This measure is defined as the distance travelled by a person over one cycle from the initial heel strike to the next heel strike.

## Clinical and cognitive (Executive Function) assessment

Unified Parkinson’s Disease Rating Scale-motor examination (UPDRS-III). UPDRS-III is a standard clinical assessment tool for the evaluation of the severity and progression of the motor-related symptoms of PD. This scale has 14 items, each scored on a 5-point Likert scale ranging from 0 to 4, with 0 representing “no impairment” and 4 representing “marked impairment”.Single-leg stance test with eyes open and closed. The participant will be asked to stand for as long as possible up to 60 s with either eyes open or closed. Trials will be terminated if the participant loses his or her balance, or if his or her feet move from the initial position. The sequence of the eyes open or closed trials will be randomized. Three trials will be performed with 3-min rest in between. This set-up was used, because this test can be used to reflect the muscle strength of the lower extremities and to test static postural stability [20].Timed Up and Go Test (TUG). The individual will be instructed to stand up from a chair, walk 3 m as quick and safely as possible, cross a line marked on floor, turn around, walk back, and sit down. The individual will be permitted to use the chair’s arm or back support for assistance when standing up, if needed [21]. The time from the “go” signal until the completion will be recorded. This test aims to measure the functional mobility used in the clinical setting.Trail Making Test Part B (TMT-B). The participants will be given a set of numbers and letters that they will be asked to connect with lines the numbers to letters in ascending order. The time consumed by the participant to complete this task will be recorded. TMT-B was used to measure processing speed and mental flexibility [22] and as a screening tool for neurological deficits such as MCI [23].Wisconsin Card Sorting Test (WCST). The participants will be given a deck of 64 cards and will be asked to sort the cards by shape, color, or number. The number of errors made and the number of successful sorted categories (maximum of 6) will be recorded. Participants will receive feedback whether the card sorted is “correct” or “incorrect”; after completing 10 consecutive sorts, the participants will switch to the next sorting category, and this process will be repeated until all the cards in the deck have been sorted. This method is frequently used as a measure of mental switching and response preservation [24].Stroop Test. The participants will be asked to name the color but not to read the word on a card. A color-word score will be given based on the total correct identification of the correct color within 45 s. The Stroop Test is a measure of how the brain process interfering signals. This test measures attention, inhibition control, and response inhibition [24, 25].

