#### Neuropsychological assessment

The three following neuropsychological assessment tools were used to examine executive functioning: Trail Making Test Part B (TMT-B), Wisconsin Card Sorting Test (WCST), and Stroop Test. These three neuropsychological assessment tools are commonly used to measure executive functioning in aging research and have been recommended as a popular screening tool for the assessment of mild cognitive impairment [29, 30].TMT-B: participants will be provided with a set of numbers and letters and will be asked to connect a line from a number to a letter in ascending order. The time that it takes the participant to complete this task will be recorded.WCST: participants will be given a deck of 64 cards and will be asked to sort the cards according to shape, color, and number. The number of errors made and the number of successful sorted categories (maximum of 6) will be recorded. Participants will receive feedback about sorting the cards as “correct” or “incorrect”. After completing 10 consecutive sorts, the participants will switch to the next sorting category and this repeated until all the cards in the deck have been sorted.Stroop Test: participants will be asked to name the color but not to read the word on a card. A color-word score will be given based on the total read in 45 s.

For the 3-D motion capture, the data will be collected and analyzed using Vicon’s *Nexus* software (v. 2.8.1) and tabulated in MATLAB (v. 7.1. Release 2006a) to obtain the temporal and spatial parameters. The functional and neuropsychological assessment measures will be gathered and stored both as hard and digital copies for further data interpretation and analysis. Descriptive analysis of the movements will be first conducted. The completion of all trials will be checked, and missing trials will be checked. For the 3D motion capture data of the participants’ movement, the data will be digitized, filtered, and processed. All *Nexus* software calculations will be derived from the Plug-in-gait model (Vicon Oxford Metrics, Oxford, UK). For each trial that will be collected, the data will be normalized to one full gait cycle. One gait cycle is defined as the succession of repeated foot-strike to the next foot-strike of the same foot. The primary outcomes will be normalized by the participants’ body height and weight.

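### The Wisconsin Card Sorting switch rule does not require correct sorts, and perseveration, a construct named for the test, has no score of its own

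*Protocol article*

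**What the plan says.** The test is described twice in the protocol article, under Clinical and cognitive (Executive Function) assessment and under Neuropsychological assessment.

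- Material: "The participants will be given a deck of 64 cards and will be asked to sort the cards by shape, color, or number".
- Feedback: each sort is called correct or incorrect.
- Switch rule, first section: "after completing 10 consecutive sorts, the participants will switch to the next sorting category". Second section: "After completing 10 consecutive sorts, the participants will switch to the next sorting category and this repeated until all the cards in the deck" is sorted. The word *correct* is missing from both.
- End of test: "this process will be repeated until all the cards in the deck have been sorted".
- Scores, in the same terms in both sections: "The number of errors made and the number of successful sorted categories (maximum of 6) will be recorded".
- Purpose, first section: "This method is frequently used as a measure of mental switching and response preservation". The last word is evidently meant to be perseveration.

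The article does not define a *successful* category and lists no perseverative score. Outcomes are measured at baseline, 6 weeks and 12 weeks.

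**The concern.** A card-sorting test measures switching because the participant must find a rule, hold it, and then abandon it when feedback changes. If the rule changes after any ten sorts, the change comes at cards 10, 20, 30 and so on, whatever the participant has done. A person who has not found the current rule is moved on just like one who has.

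This is a rule of administration as well as of scoring. The category in force decides whether the assessor says correct or incorrect on each later card, and so shapes both the participant's next response and the error total. An assessor who follows the written words and one who supplies the missing word would run different tests, and the results could not be converted afterwards.

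The second issue is the choice of scores. Total errors pools three things: persisting with the old rule, trial-and-error guesses after a change, and lapses. A group difference in that total would not show whether perseveration had changed.

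**Working it through.** **Inputs from the article:** 64 cards; 10 sorts per category; stated maximum of 6; three sorting attributes (shape, color, number). **Assumption:** the probability p that a sort is correct. The article gives none, so p runs from 0.6 to 1.0, with sorts treated as independent and p constant. No extra loss of accuracy after a rule change is modelled.

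**1. The stated maximum.** floor(64 / 10) = 6, using 6 × 10 = 60 cards and leaving 64 − 60 = 4. The figure of 6 is reproduced. It holds as an upper bound whether or not the ten sorts must be correct, so it does not show which rule was meant.

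**2. Three category counts that the text allows.**

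- A: switch after any 10 sorts, counting categories passed through. The count is 6 for everyone.
- B: switch after any 10 sorts, counting only blocks with all 10 correct. The expected count is 6 × p^10; for example 6 × 0.9^10 = 6 × 0.3487 = 2.09.
- C: switch after 10 consecutive correct sorts, counting completed runs. This was simulated with 10,000 runs of 64 cards for each p.

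| Assumed p | A: mean (SD) | B: mean | C: mean (SD) |
|---|---|---|---|
| 0.6 | 6 (0) | 0.04 | 0.15 (0.38) |
| 0.7 | 6 (0) | 0.17 | 0.49 (0.65) |
| 0.8 | 6 (0) | 0.64 | 1.39 (0.99) |
| 0.9 | 6 (0) | 2.09 | 3.16 (1.11) |
| 0.95 | 6 (0) | 3.59 | 4.43 (0.96) |
| 1.0 | 6 (0) | 6 | 6 (0) |

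The simulated means for B agree with the formula to within 0.02. At p = 0.9 the same performance scores 6, about 2 or about 3, depending on how the text is read.

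**3. Effect on the error total.** Take a participant who sorts by color throughout. Assume that color is the first category, that the three attributes rotate in fixed order, and that no card matches on two attributes at once.

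- Any-10 rule: color is in force in 2 of the 6 blocks, so 2 × 10 = 20 sorts are correct and 60 − 20 = 40 are errors, plus 0 to 4 on the remaining cards. Errors: 40 to 44. The category count is 6 on reading A and 2 on reading B.
- 10-correct rule: the first 10 sorts complete one category. The rule then leaves color and never returns, because no second run is completed. Errors: 64 − 10 = 54. Category count: 1.

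Identical behaviour gives 40 to 44 errors under one rule and 54 under the other, so both recorded scores depend on the missing word.

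**4. Recorded scores against the named construct.** Mental switching is reflected in part by categories and by total errors. Perseveration contributes to total errors and, under reading C, lowers the category count. Neither score separates it from other errors.

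**The case against.** The strongest reply is that a word was dropped and nothing more. The score is of *successful* categories, feedback on correctness appears next to the switch rule, and *consecutive* has force only if a run can be broken, which an incorrect sort would do. This is a named, cited test in a condensed article, and it is one of several secondary measures. The stated hypotheses concern gait and stability, not switching.

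Much of this stands. Correct sorts were probably intended, and the consequence is small beside the primary outcomes. But the article does set out deck, feedback, switch rule, end point and scores, and it states the switch rule the same way twice, so neither section corrects the other. The fault is in what is written, not in detail left to a fuller document.

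A reader might go further in three ways that the documents do not support.

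- *The category score is constant.* This holds only if categories passed through are counted. Reading B varies even under the literal rule.
- *The category count is a poor outcome on any reading, or the maximum of 6 is wrong.* Under reading C the count varies and sits below its ceiling over most of the assumed range. Six categories do leave only 4 spare cards against 5 rule changes, but the article gives no error cost per change, and a bound that is seldom reached is still a valid bound.
- *Perseveration is not measured.* It enters total errors. It is not scored separately, which is a narrower complaint.

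**Conclusion.** The point holds as a defect in a stated administration rule and a gap in scoring. Taken literally, the switch is independent of performance: 6 categories in 60 of 64 cards for everyone, and a count of 6 with zero variance if categories passed through are counted. The context favours ten correct sorts, but the text leaves at least three possible scores, with means of 6, 2.09 and 3.16 at an assumed accuracy of 0.9. Those means rest on constant, independent accuracy and only illustrate how far the readings diverge; they do not predict this trial's data. That the literal switch ignores performance rests on no such assumption.

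The absence of a separate perseverative score follows directly from the list of recorded scores, given that the construct named in the article is perseveration. Primary outcomes, sample size and the analysis model are untouched. The correction is worth making because it is nearly free and because data gathered under the wrong switch rule cannot be repaired.

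**What to change.** In both sections that describe the test:

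1. State that the category changes after 10 consecutive correct sorts, and that a successful category is one completed in this way.
2. Add perseverative errors, defined as sorts that follow the previous, no longer correct category, as a recorded score. Keep card-by-card responses so that it can be derived.
3. Keep total errors and categories (maximum 6) as recorded scores. There is no need to demote the category count or remove the maximum.

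If any participants have already been tested, record which switch rule was actually used and report it.

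The cost is a change of wording in two places and on the scoring sheet, slightly longer scoring, and one more secondary score. The same 64 sorts supply it, so no testing time is added.
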